# Implementation of the ERAS (Enhanced Recovery After Surgery) protocol for hysterectomy in the Piedmont Region with an audit&feedback approach: Study protocol for a stepped wedge cluster randomized controlled trial. A study of the EASY-NET project

**DOI:** 10.1371/journal.pone.0268655

**Published:** 2022-05-27

## Abstract

**Introduction:**

ERAS (Enhanced Recovery After Surgery) is a perioperative program combining multiple evidence-based interventions designed to reduce the surgical stress response. Despite the publication of dedicated guidelines, ERAS application to gynecologic surgery outside clinical studies has been slow and fragmented. To promote the systematic adoption of the ERAS program in the entire regional hospital network in Piedmont an Audit-and-Feedback approach (A&F) has been adopted within a cluster randomized controlled trial, aiming to estimate the true impact of the protocol on a large, unselected population.

**Methods:**

The study protocol provides for a multicenter stepped wedge cluster randomized trial, focused on women undergoing an hysterectomy, for comparison between standard perioperative management and perioperative management according to the ERAS protocol. The primary outcome is the length of hospital stay (LOS). Secondary outcomes are: post-operative complications, quality-of-recovery at 24-hours after surgery, 30-day readmissions, patients’ satisfaction, healthcare costs. The compliance to all the ERAS items is monitored with an A&F approach. All the gynecologic units of Piedmont hospitals are involved and all the patients hospitalized for elective hysterectomy in the period of the study are included. Centers, stratified by surgical volume and randomly assigned to four groups, are randomly ordered to activate the ERAS protocol in four periods, every three months. The planned calendar and the total duration of the study have been extended for six months due to the COVID-19 pandemic. The expected sample size of about 2400 patients has a high statistical power (99%) to detect a reduction of LOS of 1 day (effect size 0.5) and to estimate clinically meaningful changes in the other study endpoints. The study protocol has been approved by the Ethical Committee of all participating centers. Study results will be timely circulated within the hospital network and published in peer-reviewed journals.

**Conclusion:**

Results are expected to demonstrate positive clinical outcomes of the ERAS protocol even when its implementation is directed towards an entire regional network of gynecologic units, and not only towards selected and highly motivated centers.

**Trial registration:**

NCT04063072

## Introduction

ERAS (Enhanced Recovery After Surgery) is a perioperative program combining evidence-based pre-, intra- and post-operative interventions in order to reduce the surgical stress response and improve patient recovery [1].

In 2016 [2, 3] the ERAS Society developed guidelines for gynecology and gynecologic oncology surgeries that were updated in 2019 [4]. The principal items of the ERAS protocol for gynecologic surgery are reported as (S1 Table in S1 File).

Several recent studies reported that the application of the ERAS protocol to gynecologic surgery showed both clinical benefits (statistically significant reductions in hospital length of stay (LOS), opioid consumption, complications, 30-day readmissions and increased patient satisfaction) and cost savings to the healthcare system [5–8]. Moreover, some studies showed a positive dose-response relationship: the higher the adherence to the ERAS gynecology guidelines, the higher the clinical benefits [9, 10]. A recent systematic review of 31 studies (6703 gynecologic oncology patients) and meta-analysis demonstrated a decrease in LOS of 1.6 day, a 32% reduction in complications and a 20% reduction in readmission with ERAS implementation [11]. The mean cost savings for ERAS patients was $2129 USD [11].

However, validity of ERAS applied to gynecology has been questioned as available studies are based on sequential cohort designs (novel ERAS strategy against historical controls) and therefore prone to biases, including the Hawthorne effect (inadvertent introduction of an effect through the act of studying the intervention) [12, 13].

In a joint effort by the ERAS and ERAS USA societies, the Reporting on ERAS Compliance, Outcomes, and Elements Research (RECOvER) checklist was recently published [14] to provide a standardized framework for the designing and the reporting of ERAS-related studies.

A monocentric randomized study, compliant with the RECOvER checklist, was published in 2020 [15]. This study found that, compared with standard perioperative care, women in the ERAS group had a shorter LOS (median, 2 days versus 4 days), 15% less postoperative complications, and improved patient satisfaction at 24 hours and at discharge (based on the Quality of Recovery 15 questionnaire scores) [16]. The reduced LOS was confirmed in the prespecified analysis favoring the ERAS cohort in benign, malignant, open, and minimally invasive subgroups. However, the small sample size and the individual patient randomization within a single center may have limited the validity and generalizability of these findings.

In this evolving background, the application of the ERAS protocol in gynecologic surgery has been slow and limited to a minority of hospitals, at least in Italy [17] and Piedmont (a region of North West of Italy with 4.3 million population) (regional survey–unpublished data). In 2017 the diffusion of ERAS protocol in Piedmont was limited to few hospitals, particularly open to change, that had spontaneously adopted the protocol. This survey convinced the regional health authorities that, without a systematic implementation effort on the entire regional hospital network, the impact of ERAS on the overall quality on a regional scale was negligible and, possibly, a source of unjustified heterogeneity between centers and inequalities among patients.

To promote the systematic adoption of ERAS protocol in the entire regional hospital network in Piedmont an Audit and Feedback approach (A&F) was planned and a large, population based, cluster randomized controlled trial was designed to carefully estimate the effectiveness of the protocol on several quality endpoints.

The A&F strategy is recommended by the ERAS society guidelines for gynecologic/oncology surgery (quality of evidence: high; recommendation: strong) as an instrument to be applied regularly by healthcare providers when driving change or implementing ERAS programs [4].

This regional project is part of a larger project on the evaluation of the effectiveness of audit and feedback interventions (EASY-NET), a Network Project founded by the Ministry of Health and the participating Regions (NET-2016-02364191).

In this article we present the study protocol of the ERAS-Gyneco trial (http://www.clinicaltrials.gov, registration number: NCT04063072).

## Methods

### Trial design

The ERAS Protocol Implementation in Piedmont Region for Hysterectomy (ERAS-Gyneco) is a prospective multicenter cluster randomized controlled trial, with a stepped wedge design, to compare the perioperative management and outcomes before (usual care) and after the implementation of the ERAS protocol. We hypothesize that the adoption of the protocol will result in a reduction of the length of stay, complications, healthcare costs and will improve functional recovery and patient satisfaction.

Clusters are represented by all the regional hospitals with a gynecologic unit. Each cluster will progressively adopt the ERAS protocol according to a random order. At the end of the study, each unit will have a period of activity with usual procedures ("control period") and one with ERAS protocol adoption ("experimental period") with a cross-over like design, but with a single transition (from control to experimental).

The SPIRIT 2013 Checklist (https://www.spirit-statement.org/) is provided in the S1 File. Fig 1 shows the study diagram according to the CONSORT extension for Stepped Wedge Cluster Randomised Trials [18].

**Fig 1 pone.0268655.g001:**
[figure not shown]
Diagram of the ERAS-Gyneco Piemonte study with the expected number of patients in each group of hospitals and study period.

The manuscript has been prepared according to the RECOvER checklist [14] (see the S1 File).

### Study organization

The study is promoted by the “S.Croce e Carle” Hospital (Cuneo) (previous promoter, until 19/02/2020, was the “Regina Montis Regalis” Hospital—Mondovì, Cuneo). The trial design, data collection and monitoring, statistical analyses and feedback activities are under the responsibility of the Clinical Epidemiology Unit of the “AOU Città della Salute e della Scienza di Torino”—Hospital (Torino) as part of the Work Package 3 of the EASY-NET Project.

### Inclusion criteria

All gynecologic units of Piedmont Region hospitals performing at least 20 hysterectomies per year, with either laparoscopic or laparotomic approach.All patients hospitalized during the study period for elective hysterectomy for cervical or endometrial cancer or for benign uterine pathologies, with the exception of pelvic floor disorders.

### Exclusion criteria

Units with less than 20 hysterectomies per year.Patients undergoing an emergency procedure.Patients with high complexity or clinical severity, to be documented at the time of admission, which represent contraindication to the application of the ERAS protocol (e.g. patients with ASA score V).

No exclusion will be allowed for patients with social issues, who do not allow for an adequate standard of personal autonomy or post-operative home care (conditions of severe dementia, physical dysfunction, state of indigence). The presence of these conditions will be recorded in the Case Report Form, but patients will be included and managed according to the ERAS protocol anyway. Specific attention will be required for the timing of discharge, which must be decided according to patient’s needs and possibility (the date when the patient is “ready for discharge” will be recorded in the database).

### Stratification and randomization of the centers

All the gynecologic units were contacted prior to the beginning of the study to assess their level of knowledge of the ERAS protocol. Centers which already had fully adopted the protocol before the start of the study were excluded from randomization and included in an observational group to serve as an external benchmark for the study. All the other centers were stratified by the volume of hysterectomies performed during 2018 and randomly divided into 4 groups, each with a similar number of units and procedures. Then, the 4 groups were randomly ordered to activate the protocol according to a predefined calendar with 3 months interval between successive rounds. This stratified randomization was adopted to assure a more homogeneous composition of the groups for each activation period. All randomization procedures were performed by the Clinical Epidemiology unit after anonymizing the centers. The calendar date for protocol activation was communicated to each group about two months before the starting date to allow sufficient time for the training of the local ERAS team and to organize the activity.

After an initial 3-months period of data collection, performed in all centers to describe the baseline usual care, the first group of hospitals activates the ERAS protocol and then, every three months, the other groups follow step by step.

### Interventions

#### ERAS group

Each center is asked to appoint an "ERAS team", involving at least one person per professional role among gynecologic surgeons, anesthetists, nurses, and dieticians, with the aim to support the local implementation of the protocol and to be the point of reference for the center.

In the quarter preceding the date of randomization, each ERAS team receive specific training on the ERAS principles. The training consists of a one-day interactive course run by expert ERAS trainers. The selected participants are subsequently required to cascade training to their colleagues at local level. Slides are shared for this purpose and support by the expert ERAS trainers is available, if required.

#### Control group

Each center is assigned to the control group during the first three months of baseline and thereafter, until the randomization date. During the control period centers are required to continue with their usual perioperative care and to complete the Case Report Form (CRF) for the enrolled patients. Control group CRF will be analyzed to check compliance for each component of the ERAS protocol in the baseline phase and thereafter, until entering the experimental period.

#### Audit&Feedback

The study has a dedicated website (EPICLIN: https://new.epiclin.it/it/eras_isterectomia/) for data collection, data entry monitoring and feedback.

From the beginning of the study, all the centers can access the “monitoring area” on Epiclin to keep track of data collection progress and visualize graph and tables describing: number of enrolled and discharged patients, number of patients keen to participate to an interview after discharge and number of patients filling the quality of recovery questionnaire.

Once entering the experimental period, centers will also gain access to a feedback area. This area displays various graphs monitoring the indicators of compliance to all the ERAS items reported in S1 Table in S1 File. The aim is to verify the centers progress in applying the protocol in order to promptly identify low compliance issues and address them with corrective actions. Each indicator of adherence is stratified by study period (control and experimental) to appreciate changes in clinical practice. A radar graph allows to compare the adherence of groups of indicators measured in three different situations: before randomization, after randomization and in a benchmark setting (a group of regional hospitals already applying ERAS before the study).

After the first three months of ERAS adoption, the regional coordinating group organizes a workshop for each of the four groups with the expert ERAS trainers and the coordinating/data management team to discuss the feedback indicators, the critical issues encountered and to suggest possible concrete solutions to enhance compliance to ERAS protocol.

A periodic Newsletter is sent to all the ERAS teams to maintain engagement and motivation in the overall project and to share information on study progress and relevant news.

#### Primary outcome

Mean LOS, calculated after excluding patients with LOS exceeding a predefined threshold, corresponding to the 98^th^ percentile of the distribution.

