#### Secondary outcome

Percentage of LOS longer than the threshold corresponding to the 98^th^ percentile of the distributionPost-operative quality of recovery score, measured with the QoR-15 [16] questionnaire around 24 hours after surgeryIncidence of post-surgical complications, defined according to the Clavien-Dindo classification [19]Intensive care unit access in the post-operative periodPercentage of Emergency Department (ED) admissions up to 30 days after surgery (regardless of diagnosis)Percentage of readmissions to hospital within 30 days after surgery (regardless of diagnosis)Percentage of re-intervention (within 30 days after surgery)Perceived patient satisfaction score measured with the SSQ-8 [20] questionnaire via telephone interview around two weeks after discharge (only in a random sub-sample of patients keen to participate)Average healthcare costs, calculated from pre-hospitalization up to 30 days after surgeryAssessment of professionals’ satisfaction measured qualitatively.

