### Statistical plan

Fig 1 describes the sequence of randomizations of the clusters with the number of centers and the expected patients for the control and experimental periods. The total number of cases expected in 15 months is around 2400 patients (about 200 cases in the control period and 1200 in the experimental period).

Details on sample size estimation and power assessment are reported in the Supporting Information (see section “Statistical plan” in S1 File).

The main end-point, mean LOS calculated after excluding the durations greater than the threshold, will be compared between the two study periods using a random-effect linear regression model, adjusting for the time effect and the surgical technique (laparoscopic vs. open surgery). The center will be included in the model as a random effect. For dichotomous endpoints measured as proportions (e.g. length of stay above the threshold, complications, readmissions), the effect of implementing the ERAS protocol will be estimated with logistic regression models, with centers as random effects, including in the model the same set of covariates used for the analysis of the LOS.

Details on subgroup analyses and sensitivity analyses are provided in the Supporting Information (see section “Statistical plan” in S1 File).

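### The primary outcome deletes patients because of their own length of stay, so it does not estimate the effect on mean stay in all patients (should be fixed)

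*Protocol article*

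**What the plan says.** Under Primary outcome, the protocol article gives "Mean LOS, calculated after excluding patients with LOS exceeding a predefined threshold", the threshold "corresponding to the 98^th^ percentile of the distribution". The Statistical plan carries this into the main comparison: "mean LOS calculated after excluding the durations greater than the threshold, will be compared between the two study periods". The model named there is a linear mixed model with centre as a random effect, adjusted for time and for laparoscopic versus open technique. Nothing in that model accounts for the deleted patients.

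They are counted separately. The first secondary outcome is "Percentage of LOS longer than the threshold corresponding to the" same percentile, analysed by logistic regression. Complications, intensive care access, emergency visits, readmissions, re-interventions and costs are also secondary outcomes, with no exclusion by length of stay (LOS) stated.

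Two other statements bear on the choice. The Abstract says the trial aims at the true impact in a large population without selection. The Exclusion criteria forbid leaving out patients with social problems and require their discharge to be timed to their needs.

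**The concern.** The rule that removes a patient from the primary analysis is the patient's own LOS, observed after the centre has been allocated to a period. LOS is what ERAS is intended to shorten, and the Trial design section also hypothesises fewer complications. If ERAS shortens stays, more control-period than ERAS-period patients lie above a common threshold, and the longest control stays are removed selectively. If ERAS lengthened some stays, the removal would run the other way.

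The primary estimate is therefore conditional on the outcome. It compares patients who did not stay long under one policy with patients who did not stay long under the other. Some patients must be enrolled and may stay longer for social reasons, yet they leave the headline comparison if they cross the threshold.

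**Working it through.** **1. The stated power.** From the Abstract: about 2400 patients, 99% power, a 1-day reduction, effect size 0.5. The implied SD is 1 / 0.5 = 2 days. Two assumptions are needed. Two-sided alpha is taken as 0.05, which the article does not state. The split is taken as 1200 per period, because the printed 200 and 1200 do not add to 2400.

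Patients per period for 99% power under individual randomisation: n = 2(1.960 + 2.326)² × 2² / 1² = 147. With 1200 per period this leaves room for a design effect of 1200 / 147 = 8.2. The stated 99% is consistent with these inputs. The cluster calculation itself is in the supplement and was not checked.

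**2. Effect of the deletion.** The article gives no LOS distribution, so the shapes are assumptions. Two million patients per period were simulated with control mean 4 days. In the first four rows LOS is lognormal. In the others it is lognormal with SD 1.5, and a stated share of patients has 10 days added. The threshold was the 98th percentile of the pooled data or of the control period. Time and centre effects were left out. Effects are reductions in days; paired values are pooled / control-period threshold.

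| Scenario | True effect | Deleted, control vs ERAS (pooled) | Truncated mean | Capped at threshold |
|---|---|---|---|---|
| Mean 4 to 3, proportional, control SD 2 | 1.00 | 3.3% vs 0.7% | 0.83 / 0.88 | 0.95 / 0.97 |
| Mean 4 to 3, proportional, control SD 3 | 1.00 | 3.0% vs 1.0% | 0.78 / 0.83 | 0.92 / 0.94 |
| Every stay 1 day shorter, SD 2 | 1.00 | 2.5% vs 1.5% | 0.94 / 0.95 | 0.98 / 0.98 |
| Mean 4 to 3, SD 2 in both | 1.00 | 2.4% vs 1.6% | 0.97 / 0.98 | 1.00 / 1.00 |
| Only long stays change, 3% to 1% | 0.20 | 3.0% vs 1.0% | 0.00 / 0.06 | 0.16 / 0.18 |
| Only long stays change, 1% to 3% | -0.20 | 1.0% vs 3.0% | 0.00 / 0.00 | -0.15 / -0.09 |
| Typical stay 1 day shorter, long stays 1% to 3% | 0.80 | 1.1% vs 2.9% | 0.98 / 0.98 | 0.82 / 0.87 |
| No effect, 2% long stays in both | 0.00 | 2.0% vs 2.0% | 0.00 / 0.00 | 0.00 / 0.00 |

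The true values follow by hand: (0.03 - 0.01) × 10 = 0.20, and 1.00 - 0.02 × 10 = 0.80.

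**3. Sensitivity to the tail.** With a fall from 6% to 3% adding 8 days, the true effect is 0.03 × 8 = 0.24 and the truncated estimate 0.12 / 0.15. With 4% to 2.7% adding 10 days, it is 0.013 × 10 = 0.13 against 0.05 / 0.06. These errors are about 0.1 day. With a heavier tail (long stays averaging 24 days), a fall from 3% to 1% is truly 0.38 to 0.40 and is estimated as 0.00 to 0.09. In the mixed case (typical stay 1 day shorter, long stays 1% to 3%) a true 0.57 to 0.59 becomes 0.98 to 1.00.

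**4. Consequence for power.** At the worst attenuation, 0.78 day with SD 2, n = 147 / 0.78² = 242 and the design effect allowed is 1200 / 242 = 5.0. With all patients kept and SD 3, n = 147 × 9 / 4 = 331 and it is 3.6. The standard stepped-wedge variance was also applied (constant effect, four sequences, five periods, 2400 patients), with 12 to 28 centres and an intracluster correlation of 0.01 to 0.2 as assumptions. Power is at least 0.9998 for 0.78 day at SD 2, and at least 0.997 for 1 day at SD 3.

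**The case against.** Removing extreme stays is a familiar answer to skewed LOS, and calling the threshold predefined guards against a cut-off chosen from the results. If ERAS does what the trial hypothesises, the error is conservative and the test would still succeed. The single-centre randomised study cited in the Introduction found medians of 2 versus 4 days, which is a shift of the bulk and not a change confined to the tail. All of this stands, and it limits the severity.

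A reader might infer more in three ways.

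- **That truncation can create a false positive.** With no effect on LOS, both periods lose the same share and the comparison is unbiased.
- **That the plan would conceal harm.** The over-threshold, complication, intensive care, readmission and cost outcomes still show long or complicated stays. They do not put those patients back into the primary estimate.
- **That the over-threshold outcome must rest on about 48 events (2% of 2400) and is therefore underpowered.** The article does not say which distribution sets the percentile. A threshold from earlier data would not fix the trial proportion at 2%. The documents shown give no design factor for such a calculation, and a secondary outcome need not be powered.

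The supplement may contain a sensitivity analysis without truncation. This cannot be judged here, and it would not change what the primary estimate is.

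**Conclusion.** The point holds as a weakness in what the primary analysis estimates, at the level of should be fixed. The defined outcome does not give the effect on mean LOS in the whole population that the trial names.

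For effects on typical stays, the understatement is about 2% to 22% of a 1-day reduction, depending on LOS shape and threshold source, and it does not endanger power. For effects confined to long stays, most of the effect can vanish. This looks large as a percentage but is about 0.1 to 0.2 day when long stays are prolonged by 8 to 10 days, and more only with a heavier tail. The case that favours ERAS is the mixed one, where shorter typical stays come with more long ones: about 0.98 day is reported for a true 0.80.

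That the deletion depends on the outcome follows from the text alone. The sizes rest on assumed LOS distributions, and a sponsor with regional discharge data could replace them.

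**What to change.** Make the primary analysis LOS in days for all enrolled patients, in the same mixed model with robust standard errors. If outlier control is wanted, set stays above the predefined threshold equal to the threshold instead of deleting the patient. In the runs above capping kept 92% or more of a 1-day effect, though less of a tail-only effect. Keep the truncated mean as a sensitivity analysis and the percentage above the threshold as a secondary outcome. Staying on the scale of days keeps the effect in the unit for which the trial is powered.

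This changes analysis wording only and needs no new data. The cost is a larger SD: in the lognormal runs the control SD was 2.00 against 1.60 to 1.69 after truncation, and 3.00 against 2.20 to 2.34, so about 18% to 36% larger. Power for 1 day remains at least 0.997 at SD 3 under the centre numbers and intracluster correlations assumed above.
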